## **9.3. Retention and drop-out recovery**

### **9.3.1. Identifying Secondary/Proxy Contacts**

Although not a criterion for enrolment in the trial, SPRINTT will attempt to identify a proxy respondent for all participants. A proxy respondent and two additional contact persons will be identified and may be contacted to provide supplemental information on the participant.

### **9.3.2. Retention Promotion Efforts**

During the study, participants will be informed about clinically relevant test results.

Before enrolment, preventive measures will be taken to minimise participant's non-compliance related to data collection. Because the study requires a dedicated commitment to examination schedules, only those subjects who fully understand these commitments and appear likely to follow the study protocol will be enrolled. The judgment of the local study staff will be essential in determining overall eligibility with respect to adherence.

Providing clear, easy-to-follow, written instructions about when to return for follow-up visits is important. Reviewing these instructions with the participant periodically during follow-up will be a priority, especially if demonstrated compliance problems exist. Involving the subject's spouse or other family members in these reviews can be useful. Attempts will be made to maintain continuity of follow-up care, so that, whenever possible, the same staff member sees the subject throughout the study. Every attempt will be made to render all clinic visits pleasant. Minimising waiting time and facilitating transportation for the clinic assessment visits, and comfortable waiting room facilities will make the visits more pleasant, thereby enhancing participant retention in follow-up appointments. Gadgets may also be provided to study participants during the study for further enhancing adherence to the protocol.

During the follow-up phase, participants will be contacted over the phone every 6 months (mainly to retrieve information about incident health-related events) and asked to

attend clinic visits every twelve months. If they will be unable to come to the clinic, home or institutional visits as well as phone contacts might be scheduled. Telephone or proxy interviews will be scheduled if in-person visits cannot be completed. Attendance at scheduled visits will be documented by completion of specific data collection forms. Study centres are advised to keep detailed records of rescheduled and broken appointments for each participant. Participant retention will be monitored, and efforts will be made to identify those individuals who need support and encouragement. Records of participants consenting to only a portion of the follow-up procedures, i.e., partial compliance, will also be maintained. Summary reports of such difficulties will help identify problems. Critical review of such problems may offer potential solutions.

### **9.3.3. Drop-out Recovery Efforts**

The following procedures will be implemented (as appropriate in each recruitment site) to carefully document and monitor missed clinic or home visits:

- Preparing for the next visit at the end of each current visit by making the appointment and giving instructions for the next visit.
- Sending out pre-visit reminders (e.g., postcards and phone calls).
- Establishing a mechanism to chart and monitor local clinic attendance, so that clinic staff would be immediately alerted to a missed visit.
- Immediately contacting participants (usually by telephone) when they miss a visit.
- Rescheduling the visit within the same time window, if possible.

Some randomised participants will probably not actively participate in the study, perhaps by not adhering to the intervention and/or not attending the clinic. Regardless of the reason(s) for non-adherence to the study, these participants will be followed until the end of the study, and clinic staff will attempt to make contact every 6 months after the baseline assessment. These contacts will be intended to remind the participant that they are welcome to fully rejoin the study at any time. Considerable effort will be expended to collect main outcome data at appropriate times.

The following guidelines will promote adherence to the protocol, in terms of intervention adherence and clinic attendance. The availability of local clinic resources will determine which techniques should be privileged.

- Participant-staff relationship. A key element contributing to participants' continued commitment to the trial involves fostering positive, respectful relationships between study subjects and individual members of the staff.
- Continuity of care. In general, participants' appointments should be scheduled so that they can be seen by the same clinic staff members during each visit.
- Clinic environment. The clinic environment which is warm and pleasant, and oriented to the comfort of the participant.
- Participant-staff communications. Good and consistent communication is essential. Instructions are clear and interactions are friendly and individualised. The participant is reminded of the benefits of study participation. Written reminders about clinic appointments further enhance communication efforts. Unmasked clinic staff meets regularly with intervention staff to reinforce the importance of consistency of communications across intervention groups.
- Convenience and accessibility. An easily accessible clinic location, availability of transportation, and convenient clinic hours all serve to facilitate study adherence. Recruitment centres make study visits as easy as possible for participants, a factor critical to the success of the study. All sites take steps to ensure that clinic attendance is not compromised by a lack of transportation, unsuitable hours of clinic operation, or any similar circumstance. If necessary, participants are

- reimbursed for or are provided transportation to the clinic assessment visits.
- Time in clinic. Total clinic visit time is kept to a minimum, consistent with maintaining quality. If waiting is necessary, the situation is explained to the participant and, if possible, an offer is made for the participant to see another staff member, or to reschedule the visit. On the other hand, participants are not rushed or made to feel unwelcome. Clinic staff is trained to take time to visit with participants.
- Appointment reminders. Appointment reminders are used to prompt participants to come for clinic visits. These written reminders are mailed to participants so that they receive them one to two weeks before their scheduled visit date.

#### **9.3.4. Monitoring Recruitment and Retention**

The Coordinating Centre will routinely monitor screening and recruitment yields, and compare them to preset gender and SPPB score benchmarks for each site. If these benchmarks will not be attained, the main reasons for exclusion of subjects will be analyzed and the recruitment strategies accordingly modified. The Coordinating Centre will also recommend changes in the protocol, if needed. Reports on recruitment will be regularly generated and reviewed by the Steering Committee and the Data and Safety Monitoring Board.

#### **9.3.5. Retention and Efforts to Maintain Contact with Inactive Participants**

Retention is promoted by:

1. Examining and attempting to remove barriers (e.g., by addressing parking and other transportation issues, adjusting clinic hours);
2. Incorporating a variety of methods to promote contact with all participants and provide social support for all participants, including those in the HALE control arm;
3. Providing all staff and investigators who have contact with participants with training and regular re-training in motivational methods;
4. Ensuring that participants' concerns are identified and addressed before they express a desire to reduce their involvement in the study.

#### **9.3.6. Efforts to Maintain Contact with Inactive Participants**

SPRINTT has the goal of maintaining some form of contact (e.g., phone, e-mail) with participants who are unable to continue full engagement in the study and to foster some form of continued contact (e.g., even an agreement to allow future contact) with participants who are inactive in the study. The greatest importance is given to attending annual assessment visits; even participants who are unwilling to continue attending intervention sessions are strongly encouraged to attend these assessment visits.

#### **9.3.7. Monitoring and Quality Control of Recruitment and Retention**

The Data Management Centre (in close relationship with the Coordinating Centre) will collect data to monitor recruitment and retention activities, the number of potential participants contacting each site, how potential participants indicate that they heard about the study, the yield at the various screening steps, and follow-up rates. Regular web-based reports will be available to field centres and the Coordinating Centre. Regular phone contacts between recruitment sites and Coordinating Centre will be maintained in order to:

1. Review recruitment goals and yields for all centres participating on each call,
2. Review the recruitment plan and progress in achieving the objectives outlined in the plan,
3. Share successful and unsuccessful recruitment methods, and

#### 4. Review retention.

If centres encounter difficulties in recruitment, the Coordinating Centre will propose a graduated set of assistance responses based on the degree of recruitment shortfall. The possible inclusion of pre-selected back-up recruitment sites will be considered in the presence of major immitigable difficulties a centre might experience. Ad hoc amendment will be submitted in this case.

### 10. Sample size considerations and statistical analysis

#### 10.1. Sample size considerations

The primary efficacy endpoint is the time from randomization to the date of first occurrence of inability to complete the 400-m walk test in less than 15 min.

Sample size calculation is based on the LIFE study database. Specifically, survival analyses were run according to different baseline levels of SPPB score (lower than 8 vs. 8 and 9) for the primary endpoint. As depicted in Fig. 6, the effect of a long-term structured PA programme on major mobility disability was negligible in participants with baseline SPPB score  $\geq 8$  (hazard ratio = 0.94). Conversely, the hazard ratio was clinically and statistically significant in enrollees with baseline SPPB  $< 8$  (hazard ratio = 0.75; 95% CI [0.59;0.94];  $p=0.012$ ).

A total of 434 events are required to provide 85% power to detect a 25% reduction in the hazard of major mobility disability using a log-rank test performed at a two-sided alpha level of 5%. In order to achieve the 434 targeted events, 1200 subjects with baseline SPPB  $< 8$  will need to be randomised over a 12-month accrual period, with a maximal follow-up time of 3 years and a common exponential dropout rate of 25% over two years. The inclusion in the SPRINTT RCT of participants with a baseline SPPB score of 8 and above would decrease the study power and, hence, the probability of success of the trial. On the other hand, restricting the enrolment to older people with SPPB  $< 8$  would limit the aim of study to characterise the whole spectrum of PF&S. Hence, a convenience sample of 300 older adults with baseline SPPB 8 or 9 will be included in the study. An ad hoc hierarchical testing procedure has been formulated to preserve the study power (see below).

Three different plans have been developed, based on recruitment efficiency, incidence of events and length of follow-up. A blinded sample size reassessment based on number of events is planned after 11 months from the beginning of recruitment to ensure that 434 events will be reported at the end of study (3 years after the first study participant has been enrolled). This interim evaluation will allow taking immediate actions to preserve the study power in case the efficiency of enrolment or the number of observed events is not coherent with the original assumptions.

1) Scenario 1: recruitment starts at a rate of 125 participants/month (8-9 participants/centre/month). Based on a log-rank test with a 5% two-sided alpha level, a sample size of 1,500 participants (750 per treatment arm; 80% participants with SPPB  $< 8$  and 30% with SPPB  $> 30\%$ ), with a total number of 35 events at 11 months and 43 at 12 months, will provide 83% power to detect a 30% reduction in the hazard rate over 24 months of follow-up (247 events).

2) Scenario 2: recruitment progresses as outlined above, but the number of events recorded at month 11 is lower than expected. A follow-up extension (up to 36 months) should assure that the study power is preserved (at least 80%) to detect a 30% reduction in the hazard rate with a sample size of 1,500 participants. An additional power reassessment may be performed 12 months after the end of recruitment in order to establish the optimal length of follow-up, based on the number of events recorded thus far.

3) Scenario 3: recruitment efficiency is suboptimal at the very beginning and

increases over time (from 6 to 160 participants/month). The duration of the recruitment will be extended by 6 months and the follow-up of participants enrolled earlier continued beyond 24 months (the follow-up duration initially planned), up to 36 months, which will be maintained as the maximum duration of the study. A sample size of 1,500 participants will provide 85% power to detect a 30% reduction in the hazard rate, with an expected 281 total number of events at the end of the trial. At the 11-month interim evaluation, the number of enrollees is expected to be around 475, with around 9 events recorded.

**Figure 6.** Effect of a long-term structured PA programme on the onset of major mobility disability in older persons with baseline SPPB score  $\geq 8$  (A) or  $< 8$  (B).

[figure not shown]

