**Sample size**

The sample size calculation is based on the LIFE-M study database. Specifically, survival analyses were run according to different levels of SPPB score (lower than 7, 7, 8 and 9). The outcomes considered were major mobility disability (i.e., inability to complete the 400-m walk test). The effect of PA on major mobility disability was negligible in participants with a baseline SPPB score  $\geq 8$  (hazard ratio=0.94; 95% CI: 0.72-1.23;  $p=0.65$ ). Conversely, the hazard ratio was statistically significant in participants with a baseline SPPB score lower than 8 (hazard ratio=0.75; 95% CI: 0.59-0.94;  $p=0.012$ ).

A sample of 1,200 older persons with SPPB score < 8 is estimated to provide 85% power (434 events) to detect a 25% reduction in the hazard of major mobility disability over 24 months of follow-up, considering a dropout rate of 25% over 2 years and a log rank test with a 5% two-sided alpha level. An interim blinded sample size reassessment after 11 months from the beginning of recruitment will allow taking immediate actions to preserve the study power in case the efficiency of enrolment or the number of observed events is not coherent with the original assumptions.

The inclusion in the SPRINTT RCT of participants with a baseline SPPB score of 8 and 9 would decrease the study power and, hence, the probability of success of the trial. On the other hand, restricting the enrolment to older people with SPPB score lower than 8 would jeopardize the aim of project to characterise the PF&S condition. Hence, it was decided to include a convenience sample of 300 older adults with SPPB score between 8 and 9 in the study and formulate a hierarchy for comparison: first, we will compare the effects of the interventions in participants presenting an SPPB score lower than 8 and, only in case of significant result (i.e., two sided  $p<5\%$ ), the comparison will be extended to the whole study population.

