## **4. Overview of Trial Design**

### **4.1. Design**

The SPRINTT trial is a multicentre single-blind RCT involving a MCI (based on PA and nutrition counselling/dietary nutrition) versus a healthy aging lifestyle education (HALE) programme in 1,500 non-disabled, community-dwelling persons age 70 years and older with PF&S across nine European countries (14 recruitment sites across Europe).

The primary outcome (i.e., incident mobility disability) and the PA protocol adopted in SPRINTT are based on the previous experience of the LIFE study. Looking at this prior data, it is expected a limited number of primary outcome events occurring during the first months of follow-up. In order to maximise the statistical power of the analyses without modifying the maximum duration of the trial (3 years), each participant will have a different length of follow-up according to the date of his/her recruitment. In other words, the end of the follow-up will occur at the same time for all the participants. Those randomised at the beginning of the recruitment phase (12-month long) will have a longer follow-up duration (up to 3 years) compared with those included at the end of recruitment (minimum 2 years of follow-up). Hence, an average follow-up of 2.7 years (24-36 months) is foreseen.

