- A second blinded power reassessment was performed on May 7th 2018, and revealed a lower than expected number of events (215 vs. 270). Therefore, in order to maximize the probability to reach the requested number of event (434) at the end of the study, the study duration has been increased by 7 months.

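### Protocol 10.1 sets the blinded reassessment at 434 events for the primary test, but its scenarios use another effect and population and end at 247 or 281 events; the 83% power given for 247 does not reproduce

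*Combined protocol and SAP*

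**What the plan says.** Protocol 10.1 first sizes the primary test: "A total of 434 events are required to provide 85% power to detect a 25% reduction in the hazard of major mobility disability", with a two-sided 5% log-rank test. The events are to come from 1,200 people with SPPB <8, accrued over 12 months, with a maximum follow-up of 3 years. Protocol 10.2.1 and SAP 2.4.4.1 confine the primary comparison to that stratum. Section 10.1 also says that the blinded reassessment 11 months after the start of recruitment is meant to make sure 434 events are reached by the end of the study.

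The same section then gives three plans:

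- **Scenario 1:** "Based on a log-rank test with a 5% two-sided alpha level, a sample size of 1,500 participants" and 35 events at month 11 (43 at month 12) "will provide 83% power to detect a 30% reduction in the hazard rate over 24 months of follow-up (247 events".
- **Scenario 2:** recruitment as in Scenario 1 but fewer events at month 11 than expected. Follow-up is extended so that "power is preserved (at least 80%) to detect a 30% reduction in the hazard rate with a sample size of 1,500 participants". No event count is given.
- **Scenario 3:** slow early recruitment and about 9 events at the 11-month look. The plan claims 85% power for a 30% reduction, "with an expected 281 total number of events at the end of the trial".

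The Synopsis attaches the 434 events to a different follow-up: 85% power "to detect a 25% reduction in the hazard of major mobility disability over 24 months of follow-up". SAP 1.3 gives a maximum of 36 months for the same calculation.

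SAP 1.3 keeps 434 events, HR 0.75 and SPPB <8, and does not repeat the scenarios. It records that the second blinded look in May 2018 "revealed a lower than expected number of events (215 vs. 270"), after which the study was lengthened by 7 months to reach 434. SAP 1.5 says that the statistical section of the protocol was not amended, so the scenario text stands.

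**The concern.** The scenarios are the only benchmarks the protocol gives for the 11-month look, and none of them describes the confirmatory test. They change the effect (0.70 for 0.75), the population (both SPPB strata for SPPB <8) and the final event count (247 or 281 for 434). Scenario 2 is triggered when month-11 events are lower than expected, and the only expected figure for that pace of recruitment is Scenario 1's 35. Read literally, a trial exactly on Scenario 1 would trigger no extension while heading for 247/434 = 57% of the events the primary test needs.

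HR 0.70 for the whole sample also has no source in the documents. The estimates taken from the LIFE study database are 0.75 for SPPB <8 and 0.94 for SPPB ≥8, and section 10.1 itself says that including SPPB 8 and above would lower the power.

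The 83% attached to 247 events also looked too high for the stated effect and alpha.

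**Working it through.** **Inputs.** Two-sided alpha 0.05, log-rank (10.1); 1:1 allocation (7.4.3.2); HR 0.75 with 434 events (10.1, primary test); HR 0.70 with 247 and 281 events (10.1, Scenarios 1 and 3). Dropout affects how quickly events accrue, not the power for a given number of events.

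**Formula (Schoenfeld, 1:1).** Power = Φ(½·√d·|ln HR| − 1.960), where d is the number of events. Events needed: d = 4(1.960 + z_power)² / (ln HR)². Here |ln 0.75| = 0.2877 and |ln 0.70| = 0.3567.

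**Step 1: the plan's own figures.**

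| Events | HR | ½·√d·\|ln HR\| − 1.960 | Power | Stated |
|---|---|---|---|---|
| 434 | 0.75 | 2.997 − 1.960 = 1.037 | 85.0% | 85% |
| 281 | 0.70 | 2.990 − 1.960 = 1.030 | 84.8% | 85% |
| 247 | 0.70 | 2.803 − 1.960 = 0.843 | 80.0% | 83% |

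The first two reproduce; the third does not. For 83% power at HR 0.70, d = 4(1.960 + 0.954)² / 0.1272 = 267.01, so 268 events after rounding up. For 80% the formula returns 247, the count that Scenario 1 states.

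Other standard methods do not recover 83% with 247 events at HR 0.70: Freedman 79.2%, two proportions with 750 per arm 79.4%, allowance for the unequal split of events between arms 79.0%, and one-sided 5% 87.7%. By Freedman, 83% needs 273 events.

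**Step 2: the primary test at the scenario counts, HR 0.75, every event taken to be in SPPB <8.**

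- 247 events: 2.261 − 1.960 = 0.301, power 61.8%.
- 281 events: 2.411 − 1.960 = 0.451, power 67.4%.

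These are upper bounds, because the counts belong to 1,500 people and the primary test uses only the SPPB <8 stratum.

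**Step 3: part of the events in SPPB <8.** The documents give no planned split of events. I assume 80% to 90%.

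| Scenario | Share in SPPB <8 | Events in primary test | Power at HR 0.75 |
|---|---|---|---|
| 1 (247) | 80% | 198 | 52.5% |
| 1 (247) | 90% | 222 | 57.3% |
| 3 (281) | 80% | 225 | 57.8% |
| 3 (281) | 90% | 253 | 62.8% |

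**Step 4: is HR 0.70 plausible for all 1,500?** Weighting the LIFE estimates by an assumed 80% event share gives exp(0.8·ln 0.75 + 0.2·ln 0.94) = 0.78; a 90% share gives 0.77. Both are weaker than the 0.70 the scenarios use.

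**The case against.** The strongest answer is that the scenarios did not govern the trial. Section 10.1 names 434 as the purpose of the reassessment, SAP 1.3 keeps 434, HR 0.75 and SPPB <8, and the 2018 look led to an extension aimed at 434. The 270 events expected by May 2018 already exceed Scenario 1's final total (the SAP does not say which population that count covers), so 247 can hardly have been the working target. No text says to stop at 247 or 281. All of this stands, and it makes the power loss conditional.

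A reader might infer more from three places, and the documents do not support it:

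- **That 281 became the target.** The May 2017 decision (6 more months of accrual, follow-up capped at 36 months) has the form of Scenario 3's action. The SAP does not say that Scenario 3's count was used, and the 2018 look names 434.
- **That 35 events at month 11 are themselves too few for 434 at month 36, or that 24 months of follow-up each would yield a calculable shortfall.** With a constant event hazard one would expect about 101 events at month 11 in SPPB <8, and 377 in total with 24 months each. But the protocol states exponential dropout, not exponential event times, and section 4.1 expects few events in the first months. A rising hazard (Weibull shape 1.8, an assumption), calibrated to the same 434, gives 35 at month 11. The comparison is not like for like either, since the protocol's 35 counts all 1,500 people.
- **That the 83% figure causes the shortfall.** It does not. The loss comes from the change of effect size and population.

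It can also be said that both looks are past and randomisation closed in November 2017, so new 11-month benchmarks cannot alter conduct. That lowers the urgency. It does not remove the contradiction from a protocol section that was never amended.

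**Conclusion.** Two separate faults hold. First, section 10.1 contradicts itself: the target is 434 events for HR 0.75 in SPPB <8, while its scenarios end at 247 or 281 events for HR 0.70 in 1,500 people. Second, the Scenario 1 pair of 83% and 247 events is wrong by about 3 percentage points of power or about 21 events (268 − 247). The documents do not show which of the two numbers is the slip. The composition line in the same scenario gives shares of 80% and 30%, which cannot both be right, so the paragraph is unreliable as text. Scenario 3's power and count agree with each other.

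The consequence for the primary test is at most 62% or 67% power, and 53-57% or 58-63% under the assumed 80-90% event share, but only if the scenario counts were treated as enough. The documents do not show that the trial was run to those counts, and it should not be described as having been. The Synopsis also disagrees with 10.1 and SAP 1.3 on the follow-up that goes with 434 events. This should be fixed; it does not invalidate the primary analysis.

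**What to change.** 1. Restate Scenarios 1-3 for the primary test: SPPB <8, HR 0.75, 434 events. Give an event count for Scenario 2.
2. Replace the month-11 and month-12 benchmarks with expected events in SPPB <8, derived from the event-time pattern in the LIFE database.
3. Correct the 83%/247 pair to 80% with 247 events, or 83% with about 268, if it is kept at all. Correct the composition line beside it.
4. At each reassessment, state the power of the primary test at the projected SPPB <8 event count. In SAP 1.3, say which population the 215 and 270 events refer to.
5. Align the Synopsis's 24 months of follow-up for 434 events with the maximum of 36 months in 10.1 and SAP 1.3.

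If the protocol is not to be amended, the reconciliation can be stated in SAP 1.3. The cost is wording and a short recalculation, with no added participants. The downside is that some stated figures become less favourable.

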### 10.2.1. Primary efficacy endpoint

The primary comparison of intervention groups with respect to the distribution of time until the first post-randomisation occurrence of the primary outcome will be based on log-rank stratified by study site and gender. The primary comparison will be conducted only in study participants with baseline SPPB  $< 8$ . If this primary analysis is statistically significant ( $p < 0.05$ ), the comparison will be extended to include the remaining 300 participants with baseline SPPB 8-9. An additional binary indicator variable will be introduced denoting a baseline SPPB score  $< 8$  or  $\geq 8$  and its interaction with the intervention group. Hazard ratio and confidence interval will be computed for the whole population only if this interaction term can be ignored (i.e., if it is not statistically significant). The hazard ratio between intervention groups and the corresponding confidence interval will be computed using a Cox proportional hazard model with site and gender as co-variables for comparison in subjects with a SPPB score  $< 8$  and by adding

the SPPB score  $\geq 8$  flag and corresponding interaction term as co-variables for the comparison in the whole study population.

The time to event is defined as the time from randomisation to the date of first occurrence of disability. Participants who do not meet this criterion will be censored at the time of their last primary outcome evaluation. In secondary analyses, in order to take into account additional covariates, we will use a Cox proportional hazards model if the underlying assumptions appear warranted. The proportional hazards assumption will be verified by testing the treatment-by-time interaction in the Cox model.

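### Protocol 10.1 states its reassessment scenarios' power for a 30% reduction in all 1,500 participants (247 or 281 events where a count is given), which does not describe the primary test: SPPB <8, 25% reduction, 434 events

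*Combined protocol and SAP*

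**What the plan says.** Protocol 10.1 first sets the design: "A total of 434 events are required to provide 85% power to detect a 25% reduction in the hazard of major mobility disability". The test is a two-sided 5% log-rank. For that count, "1200 subjects with baseline SPPB $< 8$ will need to be randomised over a 12-month accrual period". Follow-up runs to three years at most, and dropout is taken as exponential, 25% by two years. The section says the blinded reassessment, 11 months after recruitment starts, is there to make sure 434 events are reported by the end of the study. Protocol 10.2.1 fixes the population: "The primary comparison will be conducted only in study participants with baseline SPPB" below 8. SAP 2.4.4.1 repeats that restriction.

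The same section then lists three scenarios based on recruitment, event incidence and length of follow-up. All three use 1,500 participants and a 30% reduction.

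- Scenario 1 expects 35 events at 11 months and 43 at 12 months, and "will provide 83% power to detect a 30% reduction in the hazard rate over 24 months of follow-up (247 events". It describes the sample as 80% SPPB <8 plus 30% in the other group.
- Scenario 2 promises at least 80% power for a 30% reduction with follow-up extended to as long as 36 months. It gives no event count.
- Scenario 3 extends recruitment by six months and "will provide 85% power to detect a 30% reduction in the hazard rate, with an expected 281 total number of events".

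SAP 1.3 restates 434 events, a 25% reduction and SPPB <8. It does not mention 247, 281 or a 30% reduction.

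**The concern.** A blinded reassessment needs one population, one effect size and one event target. Section 10.1 supplies two sets. The set attached to the scenarios changes all three elements together and reaches its stated powers with 57% (247/434) or 65% (281/434) of the events required for the primary test.

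The change of effect size also runs against the section's own evidence. In the earlier trial the effect was negligible at SPPB 8 or above (HR 0.94), and the section says that adding such participants would lower power. The scenarios add them and assume a larger effect. No source is given for the 30%.

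At stake is how the reassessment is read. Someone comparing the trial with the scenario figures could judge it to be on course while it was heading well short of 434 events in SPPB <8.

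**Working it through.** **Inputs.** Two-sided alpha 0.05, 1:1 allocation, log-rank test; HR 0.75 with 434 events; HR 0.70 with 247 and 281 events (all Protocol 10.1). SPPB <8 is 80% of enrolment, 1,200 of 1,500 (Protocol 9.1).

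**Formulas (Schoenfeld).** Power = Φ(√(D/4) × |ln HR| − 1.960). Events required = 4(1.960 + z_power)² / (ln HR)². Here ln 0.75 = −0.2877 and ln 0.70 = −0.3567.

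**1. The plan's own figures**

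- 434 events, HR 0.75: √108.5 × 0.2877 − 1.960 = 1.037, power 85.0%. Stated 85%; reproduced.
- 281 events, HR 0.70: √70.25 × 0.3567 − 1.960 = 1.030, power 84.8%. Stated 85%; reproduced.
- 247 events, HR 0.70: √61.75 × 0.3567 − 1.960 = 0.843, power 80.0%. Stated 83%; not reproduced.

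Other methods do not rescue the 83%. Freedman gives 79.2%, a Wald version with unequal events per arm gives 78.8%, and a one-sided test gives 87.7%. The count for 83% at HR 0.70 is 4(1.960 + 0.954)² / 0.1272 = 267.0, or 268 if rounded up to be safe. The figure of 247 is the Schoenfeld count for 80%. Separately, 80% + 30% = 110%.

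**2. Power of the primary test at the scenario counts (SPPB <8, HR 0.75)**

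| Scenario | Share of events in SPPB <8 | Events | Power |
|---|---|---|---|
| 1 | 100% (upper bound) | 247 | 61.8% |
| 1 | 80% (assumed) | 0.8 × 247 = 197.6 | 52.5% |
| 3 | 100% (upper bound) | 281 | 67.4% |
| 3 | 80% (assumed) | 0.8 × 281 = 224.8 | 57.8% |

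For comparison, 80% power at HR 0.75 needs 380 events. Scenario 2 gives no count; its floor of 80% at HR 0.70 corresponds to 247.

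**3. Does shorter follow-up explain the lower counts?** Assume constant hazards, uniform accrual over 12 months, dropout rate δ = −ln(0.75)/24 = 0.0120 per month, and no delay from visit timing. Expected events per arm are (N/2) × the average over entry times of [λ/(λ+δ)] × [1 − exp(−(λ+δ)f)], where f is the time followed.

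- 434 events in 1,200 by month 36 require a control hazard of 0.0212 per month, a two-year control rate of 1 − exp(−24 × 0.0212) = 40%.
- At that hazard, capping each participant at 24 months gives 377 events, and stopping 24 months after the first enrolment gives 305. Both exceed 247, and from 1,200 participants rather than 1,500.
- Conversely, 247 events in 1,500 at HR 0.70 imply a two-year control rate of about 19% to 27%, depending on how the 24 months are read.

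So the two parts of the section also rest on different event rates. By month 11 the 434-event design would give about 101 events under this model, against 35 in Scenario 1. The 101 is probably too high: Protocol 4.1 expects few events in the first months, and the same model over-predicts Scenario 1's own count (51 to 79 against 35). The comparison shows only that the month-11 benchmark was not derived from the 434-event design.

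**The case against.** The strongest reply is that the scenario counts were never the target. The paragraph introducing the scenarios names 434 as the purpose of the reassessment, and nothing authorises ending the trial at 247 or 281.

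The SAP bears this out. SAP 1.3 restates the 434-event basis. It reports that the first reassessment lengthened accrual by six months, the same operational step as Scenario 3 but without its 281 events. It also reports that the second found 215 events against 270 expected and lengthened the study by seven months to reach 434. The 270 expected at that intermediate look already exceeds Scenario 1's final 247, although the SAP does not say which SPPB group those counts cover. The primary test, its population, its alpha and its event target are consistent in Protocol 10.1, 10.2.1 and SAP 1.3, 2.4.4.1 and 2.4.4.3. All of this stands, and it limits the practical consequence.

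Two further points stand. The share of events in SPPB <8 is not given. That group is described as the frailest (Protocol 5.3.1), so its share could exceed 80%. And the 80%/30% split is evidently a slip, since Protocol 5.3.1, 7.4.3.2 and 9.1 all give the 80% share.

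The reply does not remove the contradiction. The scenario powers remain in the protocol as the figures that accompany the reassessment, and SAP 1.5 says the protocol's statistical section was not amended.

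**Conclusion.** The concern holds as an internal contradiction in Protocol 10.1 that should be corrected. It is not a defect in the primary analysis. The scenario powers of 83%, at least 80% and 85% do not describe the primary test, and the 83% is wrong even on its own basis.

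Power of the primary test at the scenario counts would be 52% to 62% for Scenario 1 and 58% to 67% for Scenario 3, against 85% at 434 events. The upper ends assume every event falls in SPPB <8; the lower ends assume 80% do. All take HR 0.75 as true.

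Three stronger readings are tempting, and the documents do not support them.

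- A reader might infer that the final analysis had only 52% to 67% power. The loss arises only if the trial ended at the scenario counts, and the SAP worked to 434. Joining the two ranges also mixes two scenarios with two assumptions.
- A reader might infer that all three scenarios accept a reduced event count. Scenario 2 states none.
- A reader might blend HR 0.75 and HR 0.94 into a planned whole-sample effect. HR 0.94 is a result observed in the earlier trial. No effect is planned for the SPPB 8-9 group, which Protocol 10.1 calls a convenience sample.

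**What to change.** Either of two changes would do.

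1. Restate the scenarios for the primary test: SPPB <8, HR 0.75, target 434. For each, give recruitment, expected SPPB <8 events at month 11 and at the end, and the resulting power or the follow-up needed to reach 434. State the event rate assumed, and give Scenario 2 a count.
2. Keep the HR 0.70 whole-sample figures, label them as not applying to the primary test, and say where the 30% comes from. A sentence in SAP 1.3 could also record that the reassessments used 434 and not the scenario counts.

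In either case, change 83% to 80% for 247 events (or give 267 to 268 events for 83%) and correct the SPPB split to 80% and 20%.

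The direct cost is recalculation and wording. The restated powers will be less favourable. If the lower event rates implied by the scenarios are realistic, reaching 434 events in SPPB <8 would take longer follow-up or more participants, so the first option should not be presented as free.
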